**Methods:**

The planned single-blinded randomised controlled trial study was approved by the ethics committee of the German Sport University on June 14, 2022 (ethics application no. 093/2022) and prospectively registered (DRKS-ID: DRKS00030312; date of registration: 26.09.2022). *N* = 114 participants between 16 and 60 years of age with a unilateral ACL rupture and scheduled ACL reconstruction with a hamstring or quadriceps tendon autograft will be randomly (block-randomisation, 1:1 allocation) and blinded assigned to one of two groups: intervention group (structured, criteria-based, guided prehabilitation training) and comparator group (non-guided, self-administered home training). After surgical reconstruction, patients of both groups participate in the same standard, functional measurement-guided, postoperative rehabilitation programme. Stepwise increasing the functional requirements of the assessments, all participants participate in testing at the day of anamnesis (t1), 1–7 days before surgical reconstruction (t2), day of surgical reconstruction (t3) and 30 (t4), 60 (t5), 90 (t6) and 180 (t7) days post-reconstruction.

The primary outcome is the overall self-reported knee condition, assessed by the sum score of all sub-scales of the Knee injury and Osteoarthritis Outcome Score (KOOS). Secondary outcomes include functional outcomes (range of motion, knee flexors and extensors and plantar flexors strength/torque, functional postural control, jumping ability), workability and return to sport (RTS) (psychological readiness, RTS success).

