**Discussion:**

The planned study targets to fill a gap in the evidence regarding effective designs of prehabilitation training before surgical ACL reconstruction. Potential difficulties that could affect the conduct of the study are lack of treatment adherence of the patients and high dropout.

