### Sample size determination

The sample size calculation is based on the sum score of the KOOS (primary outcome parameter). The difference in the KOOS score of the comparator and intervention group at the measurement pre-reconstruction will be compared. The minimal clinically important change (MIC) for the KOOS score is reported to be a change of 8–10 with respect to the subscale score in patients with knee injuries [36]. For performing a sample size calculation, usually, a standard deviation of SD = 15 is used for the KOOS score [16]. On this basis, an effect size of *d* = 0.533 was calculated using G*Power [37]. With a power of 80% and a one-sided alpha error level of 2.5%, data must be collected from *n* = 114 participants (equal number of participants in comparator and intervention group of *n* = 57 participants).

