### Statistical analysis

The two-sided alpha-error threshold will be set at 5% for all inference statistical analyses: all p-values below this value will be considered as statistically significant. All statistical analyses will be performed using R statistic (R version 4.2.3 or newer). We will follow the CHAMP statement when designing and reporting the statistical analysis [38].

Baseline data will be displayed as means and standard deviations, while the main outcome data will be displayed as means and 95% confidence intervals.

Following plausibility control (physiological range check, formal outlier analysis), the main analyses will be conducted based on the intention-to-treat principle. For that purpose, a multiple imputation, assuming missing completely at random and using chained equations in a fully conditional specification with 40 iterations to produce asymptotically unbiased estimations of the data, will be performed.

The group affiliation of the participants (intervention group: prehabilitation, comparator group: home training) will be defined as a between-subject factor. The main analyses are calculated as linear mixed models for repeated measurements. Main inference statistical analyses will be performed using each outcome’s change scores from baseline to each follow-up as the dependent variable. These analyses will be performed confirmatory. The time effects (repeated measures) will be modelled as random effects (and factors), and the other independent variables (group) and covariates (potential confounders and effect modifiers) as fixed effects. In the same model, the influence on the treatment effect by clinically important confounders and effect modifiers age, gender, and activity level will be calculated.

Patients, who do not have surgery, will not be included. If patients will decide after inclusion that they do not want surgery after all, the last testing will be done before the originally scheduled surgery date (intention-to-treat).

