### Drop out

In preoperative training programmes that have already been implemented, participant’s compliance was high and the dropout rate was low [39–41]. Nevertheless, there is a risk of dropout in the planned study because the last testing takes place a long time after ACL reconstruction (180 days postoperative). The dropout of the study participation by the patients could distort the results. To keep the drop-out rate low, patients are regularly reminded of their testing dates, and after the testing, they receive their personal test results, which are helpful in assessing the rehabilitation process.

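### The 114 patients to be randomised equal the number whose data the power calculation needs, so the stated 80% leaves practically no room for loss before the preoperative primary assessment

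*Protocol article*

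**What the plan says.** Under Sample size determination, the protocol article bases the calculation on the KOOS sum score at the pre-reconstruction measurement. It quotes an important change of 8–10 points, takes SD 15 and arrives at d = 0.533. It then states "With a power of 80% and a one-sided alpha error level of 2.5%, data must be collected from" 114 participants, 57 in each group.

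The abstract (Methods) uses the same number for enrolment: "114 participants between 16 and 60 years of age with a unilateral ACL rupture and scheduled ACL reconstruction", who "will be randomly (block-randomisation, 1:1 allocation) and blinded assigned to one of two groups". No loss rate, inflation or reason for having none is given.

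The abstract (Discussion) lists as potential difficulties "lack of treatment adherence of the patients and high dropout". The Drop out section explains that "there is a risk of dropout in the planned study because the last testing takes place a long time after ACL reconstruction". The sentence before that one says that dropout was low in earlier preoperative programmes, without a figure.

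Outcomes sets the primary time point at 1–7 days before reconstruction (t2). Statistical analysis plans multiple imputation, with change scores from baseline as the dependent variable. It names age, gender and activity level as confounders and effect modifiers; baseline KOOS is not named.

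**The concern.** One number serves two purposes: the patients who enter the trial and the patients whose primary value must be in hand. These agree only if nobody is lost before t2.

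Loss by then is possible. Consent can be withdrawn at any time (Recruitment). The t2 assessment is a separate session of functional tests and questionnaires after at least three weeks of training (Study procedure). The closing lines of Statistical analysis say that patients without surgery are not included, and then that they are tested before the scheduled surgery date, so their status is not fully clear.

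If some t2 values are missing, the trial has less than its advertised power, and a null result would be read as coming from an 80%-powered trial when it did not.

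**Working it through.** **Inputs.** From Sample size determination: SD 15, d = 0.533 (so the difference is 0.533 × 15 = 8 points, the lower end of 8–10), one-sided alpha 2.5%, power 80%, 57 per arm. Statistical analysis says "The two-sided alpha-error threshold will be set at 5% for all inference statistical analyses"; this has the same upper critical value, so the differing wording does not affect the result.

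**Formula.** For a two-sample t-test with n per arm, the noncentrality is (difference/SD) × √(n/2) on 2n − 2 degrees of freedom. Power is the probability that this noncentral t exceeds the 97.5% point of the central t.

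**Reproducing the plan's figure.**
- n = 57: noncentrality 0.5333 × √28.5 = 2.847, critical value 1.981, power 80.6%.
- n = 56: noncentrality 0.5333 × √28 = 2.822, critical value 1.982, power 79.9%.

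So 57 per arm is the smallest equal-arm number that reaches 80%, and 114 includes no allowance for loss. With one patient lost (57 and 56) power is 80.2%. It first falls below 80% at two losses, one per arm.

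**Power under loss by t2.** The article gives no rate, so the rates below are assumptions, taken to whole patients per arm.

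| Assumed loss | Evaluable per arm | Power for 8 points | Difference detectable with 80% power |
|---|---|---|---|
| none | 57 | 80.6% | 7.9 |
| about 5% | 54 | 78.4% | 8.2 |
| about 10% | 51 | 76.0% | 8.4 |
| about 20% | 45 | 70.6% | 9.0 |

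**Effect of the analysis model.** The table treats 15 as the SD of the quantity compared. The planned dependent variable is a change score. If 15 is the SD at each time point and r is the baseline–t2 correlation (not in the article, so assumed), then:
- unadjusted change score: SD = 15 × √(2(1 − r));
- adjustment for baseline: residual SD = 15 × √(1 − r²).

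With 51 per arm and a difference of 8:

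| r | Change-score SD | Power | Adjusted SD | Power |
|---|---|---|---|---|
| 0.3 | 17.7 | 62% | 14.3 | 79.8% |
| 0.4 | 16.4 | 68% | 13.7 | 83% |
| 0.5 | 15.0 | 76% | 13.0 | 87% |

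The unadjusted change score gives the simple calculation's 76% only at r = 0.5. Adjustment at about 10% loss regains 80% once r is slightly above 0.3. The one degree of freedom spent on the covariate is ignored.

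**The case against.** The strongest objection is about timing. A reader might infer that the article's own dropout warning contradicts its sample size. The Drop out section ties the risk to the 180-day test, and a patient who leaves after t2 has already supplied the value on which the 80% rests. The same section's only remark on preoperative programmes is that dropout was low, and it adds reminders and feedback of results. This stands: the 180-day warning is not evidence about loss at t2. The remark on low dropout, however, carries no figure and is not used to justify an allowance of zero.

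A reader might also infer that any loss at all makes 80% untrue. It does not: one loss leaves 80.2%, and about 5% loss costs roughly two points. Losses of 15–20% over a short preoperative period have no support in the text.

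The calculation takes the lower end of the 8–10 point range. With 45 per arm, power for 9 points is still 80.4%. That softens the consequence but does not make the stated figure for 8 points correct.

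Finally, multiple imputation keeps every randomised patient in the analysis. It does not by itself restore the information in a missing primary value, and the sample size section itself speaks of data that must be collected.

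**Conclusion.** The point holds in a limited form. The arithmetic is right, but 114 is the evaluable number and is also the number randomised, so 80% is delivered only with practically complete KOOS data at t2. The shortfall is small up to about 5% loss (78%). It becomes material from about 10% (76%, detectable difference 8.4 points) and reaches about 71% and 9.0 points at 20%. All of these rates are assumptions. They apply to loss up to t2 alone; the article states no power for the later visits.

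The 76% is itself conditional. Under an unadjusted change score with SD 15 at each time point, power with 51 per arm would be 62% to 76% over assumed correlations of 0.3 to 0.5. The document does not settle that correlation.

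**What to change.** Keep N = 114.

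1. In Sample size determination, say that 114 is the number randomised, give the expected loss by t2 (or justify none), and restate the power that remains under the planned analysis, with the assumed SD and correlation. This costs a sentence or two and probably a less favourable figure.
2. In Statistical analysis, add baseline KOOS as a covariate in the primary model. KOOS at baseline is already needed for the change score, so this requires no new data and no extra patients. It is a change to the analysis model, so it should be made as a dated amendment before outcome data are examined. It offsets a loss of about 10% only if the baseline–t2 correlation is slightly above 0.3 or higher, and the restated power should say which value was assumed.

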### Randomisation procedure

Participants will be randomly assigned to intervention or comparator group with a 1:1 allocation as per a computer-generated randomisation schedule using permuted blocks of random sizes. The block sizes will not be disclosed, to ensure concealment. All patients who give consent for participation and who fulfil the inclusion criteria will be randomised. Allocation concealment will be ensured, as the physician at the hospital will see the randomisation code not until the patient has been recruited into the trial. The physician will see the allocation after opening the opaque sealed envelopes.

### Data processing

The data collected (paper pencil, functional test results and questionnaires) are manually transferred to an electronic database (Excel, Microsoft Office Professional Plus 2019) and checked (range data check, outlier analysis) by the study management using R statistic (R version 4.2.3). Only employees involved in the study have access to the data. Collected data are treated confidentially, pseudonymized and evaluated exclusively scientifically. The data sets used and/or analysed in this study will be chaired open access in a publicly available data repository (Zenodo) at the end of the study period. A Data Monitoring Committee is not considered as this is a low-risk intervention.

### Statistical analysis

The two-sided alpha-error threshold will be set at 5% for all inference statistical analyses: all p-values below this value will be considered as statistically significant. All statistical analyses will be performed using R statistic (R version 4.2.3 or newer). We will follow the CHAMP statement when designing and reporting the statistical analysis [38].

Baseline data will be displayed as means and standard deviations, while the main outcome data will be displayed as means and 95% confidence intervals.

Following plausibility control (physiological range check, formal outlier analysis), the main analyses will be conducted based on the intention-to-treat principle. For that purpose, a multiple imputation, assuming missing completely at random and using chained equations in a fully conditional specification with 40 iterations to produce asymptotically unbiased estimations of the data, will be performed.

The group affiliation of the participants (intervention group: prehabilitation, comparator group: home training) will be defined as a between-subject factor. The main analyses are calculated as linear mixed models for repeated measurements. Main inference statistical analyses will be performed using each outcome’s change scores from baseline to each follow-up as the dependent variable. These analyses will be performed confirmatory. The time effects (repeated measures) will be modelled as random effects (and factors), and the other independent variables (group) and covariates (potential confounders and effect modifiers) as fixed effects. In the same model, the influence on the treatment effect by clinically important confounders and effect modifiers age, gender, and activity level will be calculated.

Patients, who do not have surgery, will not be included. If patients will decide after inclusion that they do not want surgery after all, the last testing will be done before the originally scheduled surgery date (intention-to-treat).

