##### Neuromuscular control/activation

During the anamnesis, 1–7 days before the surgical reconstruction, on the day of the surgical reconstruction and 30 days after the surgical reconstruction, the participants are asked to perform an active extension of the leg while sitting (long sitting), i.e. to lift the extended leg from a mat (active stretch lifting = active lifting of the extended leg). The physician or therapist performing the test evaluates the performance as “not possible”, “possible with help” or “possible alone”.

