##### Strength/torque (knee flexors and extensors, plantar flexors)

The strength of the knee flexors (hamstrings) and the knee extensors (m. quadriceps) is recorded 90 and 180 days postoperative using a strength test on the isokinet in a range of motion of 0°–90° (ROM 0°/0°/90°). For this purpose, maximum strength capacity is tested with 5 repetitions at 60°/s and strength endurance with 15 repetitions at 180°/s.

The strength of the plantar flexors (m. gastrocnemius) is tested with the “heel lift”. The participants stand upright with their legs extended and lift their heels off the floor to the maximum. Then one foot is lifted off the ground (single-leg stand) and the participants lift the heel off the ground maximally (plantar flexion). This test is performed both preoperatively (1–7 days before surgery) and postoperatively (after 60, 90 and 180 days). After 20 repetitions in full range of motion, the test is terminated. The therapist notes the number of repetitions the participant has completed in a side-by-side comparison (right/left) if the required number of 20 repetitions has not been reached.

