##### Workability

In order to record the workability, the number of days absent from work is determined preoperatively and postoperatively. In addition, it is determined when the participants state that they are fully able to work again.

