##### Return to sport — success

The RTS success is characterised by achieving the pre-injury level of sports participation as defined by the same type, frequency, intensity, and quality of performance as before the injury.

The participant’s activity level is assessed at an initial presentation at the hospital (anamnesis), 1–7 days prior to surgery and 30, 60, 90 and 180 days postoperatively using the Tegner score (11-point scale). The Tegner score was developed specifically to assess the activity level of participants with ACL injuries and rates it on a scale from 1 (low activity level) to 10 (professional level) [33–35].

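### The only model named, a linear mixed model on change from baseline, does not fit time to full work ability, return-to-sport success or the leg-lift grade, and patients not back at work by day 180 have no stated handling

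*Protocol article*

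**What the plan says.** The Statistical analysis section of the protocol article sets one rule. It names the model family: "The main analyses are calculated as linear mixed models for repeated measurements". It then fixes what is modelled, for all outcomes alike: "Main inference statistical analyses will be performed using each outcome’s change scores from baseline to each follow-up as the dependent variable". The section labels this work confirmatory. For absent values the only rule is "a multiple imputation, assuming missing completely at random and using chained equations in a fully conditional specification with 40 iterations".

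The Outcomes section defines endpoints of several types:

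- **Workability:** days absent from work before and after surgery, and an event time: "In addition, it is determined when the participants state that they are fully able to work again".
- **Return to sport — success:** "The RTS success is characterised by achieving the pre-injury level of sports participation". The same section has the Tegner score recorded at anamnesis, 1–7 days before surgery, and at days 30, 60, 90 and 180.
- **Neuromuscular control/activation:** "The physician or therapist performing the test evaluates the performance as" one of three ordered grades (not possible, with help, alone). It is graded from anamnesis to day 30.
- **Strength/torque (heel lift):** "After 20 repetitions in full range of motion, the test is terminated". The number of repetitions is noted when 20 is not reached.

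Monitoring ends 180 days after surgery (Postoperative rehabilitation programme). The Discussion accepts that some participants may not have returned to sport by the last test.

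**The concern.** The rule is written for each outcome, yet the article's own endpoint definitions include a single event time, a yes/no result, an ordered rating and a count with a ceiling. This is a stated rule that fits some endpoints badly, so an analysis plan that follows it would carry the misfit forward under a confirmatory label.

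The event time matters most. A patient still not fully able to work at day 180 has no date because recovery is slow. That is censoring, and it carries information about the outcome. The article gives no censoring rule, and its one rule for absent values assumes they are missing completely at random. Applied here, that rule would give slow returners dates modelled on patients who did return, and the group difference would be understated. Work ability and return-to-sport success are both named among the secondary outcomes in the abstract.

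**Working it through.** **The plan's own figure.** With a difference of 8 and SD 15 (Sample size determination), d = 8/15 = 0.533. At one-sided 2.5%, the noncentral t distribution gives power 0.799 with 56 per arm and 0.806 with 57, so 2 × 57 = 114 reproduces. It concerns the KOOS only and does not bear on this point.

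**Can the stated dependent variable be formed?**

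| Endpoint | Form | Change from baseline, repeated? |
|---|---|---|
| KOOS | score | fits |
| Tegner | ordered 11-point score, measured from anamnesis on | yes, as an approximation |
| Time to full work ability | one event time | no baseline, no repeats; cannot be formed |
| Return-to-sport success | yes/no | with nobody successful at baseline, change equals the follow-up value; poor fit |
| Leg lift | three ordered grades | can be formed, but grade differences have no unit |
| Heel lift | count stopped at 20 | difference in capped counts is well defined but attenuated |

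The heel lift also has no anamnesis value. That is a separate matter: the mismatch of type would remain if every baseline existed.

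**Size for time to full work ability.** The article gives no return-to-work figures, so these inputs are assumptions: Weibull times, shape 1.5, medians 90 and 120 days, follow-up to 180 days.

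- Scale λ = median / (ln 2)^(1/1.5) = 114.9 and 153.2.
- Not back at day 180: S(180) = exp[−(180/λ)^1.5] = 0.141 and 0.280, or about 8 and 16 of 57.
- Restricted mean = ∫₀¹⁸⁰ S(t) dt = 96.1 and 115.9 days. Difference 19.8.
- Mean among returners = [restricted mean − 180·S(180)] / [1 − S(180)]. First arm: (96.1 − 25.3)/0.859 = 82.3. Second arm: (115.9 − 50.4)/0.720 = 90.9. Difference 8.6.

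With exponential times instead:

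| Back by day 180 | Restricted-mean difference (days) | Difference among returners (days) |
|---|---|---|
| 90% vs 95% | 13.3 | 7.6 |
| 80% vs 90% | 19.1 | 8.7 |
| 70% vs 85% | 24.0 | 9.2 |
| 60% vs 80% | 28.4 | 9.6 |

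The returners-only column stands in for imputation that draws from returners in the same arm. No multiple imputation was run.

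**Size for the heel lift.** Assumptions: true difference 3 repetitions, uncapped SD 7. With a = (20 − m)/SD, the capped mean is m·Φ(a) − SD·φ(a) + 20·[1 − Φ(a)].

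| Comparator true mean | 16 | 20 | 24 |
|---|---|---|---|
| Capped difference | 1.9 | 1.2 | 0.65 |
| SD after capping | 4.9 | 3.6 | 2.3 |
| Standardised effect (uncapped 3/7 = 0.43) | 0.39 | 0.35 | 0.28 |
| Loss on standardised scale | 9% | 19% | 34% |
| Power, capped count, 57 per arm | 0.55 | 0.46 | 0.32 |
| Power, 20 reached yes/no | 0.43 | 0.45 | 0.37 |

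The power rows are simulated; a closed-form check agrees within 0.02. Reducing the count to yes/no loses power at 16, changes little at 20 and gains slightly at 24.

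**The case against.** The strongest reply is about scope. The section speaks of main analyses and repeated measurements, and a single return-to-work time is not repeated, so the text could be read as not covering it. Models for non-continuous secondary endpoints are also often left to an analysis plan, which is not shown here. This has some force, but the wording that takes in each outcome and each follow-up speaks against it, and no second model is mentioned.

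Four stronger readings are tempting, and the documents do not support them.

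- **Patients not back at work by day 180 will be imputed.** A reader might infer this, but no section says how they are coded. It is what would follow if the one stated rule for absent values were applied to them.
- **Work ability as a whole is compromised.** It is not. Days absent from work are recorded too, and a patient still off work at day 180 has an observed count up to that date.
- **Return-to-sport and leg-lift results would be undefined.** If nobody is successful at baseline, the group coefficient from a linear model of success is a risk difference. The repeated Tegner score remains usable. Scoring three ordered grades linearly is a debatable approximation.
- **The heel-lift cap destroys most of the effect.** In raw repetitions the loss is 37% to 78%, but the cap also shrinks the SD, and the standardised loss is about 9% to 34%. The cap belongs to the test itself, not to the model.

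**Conclusion.** The point holds in a limited form. One confirmatory rule is stated for every outcome, and it does not suit three of the secondary endpoints the article defines. For time to full work ability the stated dependent variable cannot be formed. For return-to-sport success and the leg lift it can be formed but fits poorly.

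The practical risk is conditional on the imputation rule being applied to patients not yet back at work. In that case a restricted-mean difference of about 20 days could appear as about 9 under the Weibull assumptions, or 13 to 28 days as about 8 to 10 under the exponential ones. These are illustrations on assumed distributions, not predictions for this trial. The heel-lift ceiling is a lesser matter. The KOOS primary analysis and the sample size of 114 are not affected, so this should be corrected but does not threaten the trial's main conclusion.

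**What to change.** Amend the Statistical analysis section before results are seen:

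1. Limit the change-score linear mixed model to continuous or score outcomes: the KOOS, and the Tegner score as an acceptable approximation.
2. Analyse time to full work ability as time-to-event or as a restricted mean to day 180, censored at day 180 or last contact. State that no date is imputed for a patient known not to be back.
3. Analyse return-to-sport success at day 180 by logistic regression or risk difference.
4. Analyse the leg lift by ordinal regression adjusted for the grade at anamnesis.
5. For the heel lift, record 20 when the test is completed and treat 20 as a ceiling, for example as right-censored. Do not replace the count by a yes/no endpoint.

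The cost is analysis wording and a few lines of R, with no new visits or patients. The drawback is that secondary results will be reported on different scales.

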## Methods

### Aims

The planned study focusses on optimal content (criteria-based programme), general setting of preoperative training and supervision (one-on-one guidance or self-administered training). With this randomised-controlled trial, our objective is to compare the effects of a guided, structured and criteria-based preoperative rehabilitation programme, which can be adapted to the individual performance level, to a non-guided and self-administered home-based training programme on functional and self-report outcomes and secondary issues (other knee function, daily living and return to sport). The KOOS sum score (Knee Injury and Osteoarthritis Outcome Score) is the primary outcome and assesses the self-perceived knee function [15, 16]. We hypothesise that the guided prehabilitation programme will be more effective than self-administered home training relating to its effect on the baseline to pre-reconstruction change score of the KOOS sum score.

We will investigate the effects of pre-operative training (guided vs. unguided) at different time points (pre-op, 30/60/90/180 days post-op). We expect that the guided prehabilitation programme will have a particularly positive short-term effect and that the difference between the two groups will decrease over the progress of rehabilitation.

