##### Dynamic postural control

The dynamic postural control is measured by the Y-balance test. The Y-balance test is a functional and unilateral dynamic balance test in a single-leg stance and is performed by participants 1–7 days before surgery and 60, 90 and 180 days postoperative. It checks the range of motion of the playing leg in the three directions anterior, posteromedial and posterolateral (mobility of the joints: knee joints, hip joints, ankle joints) [26], the strength of the lower extremity [27], the proprioception [27], the dynamic balance [28] and the neuromuscular control, postural control, postural stability, as well as the trunk stability [27, 29]. The best values from both sides (left/right) and each direction (anterior/posteromedial/posterolateral) are selected from the valid trials and a total score is calculated. If the total score for one of the legs or for both legs is lower than 94%, there is an increased risk of injury [29]. The total scores (left/right) are used for further calculation of the LSI. The LSI (limb symmetry index) is used to determine whether a deficient lateral deviation is present [30].

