##### Jumping ability

Counter Movement Jump is used to assess jumping abilities in a slow lengthening-shortening cycle. It is performed at 90 and 180 days postoperative and tests the explosive power, the maximum strength and the vertical bounce [31]. With the aid of a force plate, the flight time and the impulse during the jump are determined so that the jump height can be calculated. In addition, the force development is recorded in relation to the body weight as well as the percentage difference of the maximum force development in the bilateral comparison of the legs (affected vs. unaffected leg).

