#### Return to sport

##### Psychological readiness

The ACL-Return to Sport Injury Scale (ACL-RSI) is used to assess self-confidence, risk assessment, and emotions related to the ACL injury as well as complaints and problems caused by the knee joint injury. Participants answer a total of 12 questions on the 10-point scale from 0 to 100 1–7 days before surgery and 30, 60, 90, and 180 days postoperative [32]. A total score is determined from the results of the 12 questions answered (score achieved/number of questions). If the total score is below 51%, this indicates a lack of confidence in the knee joint. The decision to return to sport after an ACL injury is significantly related to response on the ACL-RSI scale [32].

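### Change from baseline is prescribed for every outcome, but five secondary outcomes have no baseline measurement, so the stated confirmatory analysis cannot be run for them

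*Protocol article*

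**What the plan says.** All references are to the protocol article.

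The Statistical analysis section sets one dependent variable for the main analyses of each outcome: "change scores from baseline to each follow-up as the dependent variable". It then adds: "These analyses will be performed confirmatory". No exception and no alternative dependent variable is given.

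The Aims section shows what baseline means. The primary hypothesis concerns the "baseline to pre-reconstruction change score of the KOOS sum score", so baseline comes before the pre-reconstruction visit t2 and must be t1.

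The outcome sections set these visits for the five outcomes at issue:

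- Isokinetic knee strength "is recorded 90 and 180 days postoperative using a strength test on the isokinet".
- Heel lift: "This test is performed both preoperatively (1–7 days before surgery) and postoperatively (after 60, 90 and 180 days").
- Y-balance "is performed by participants 1–7 days before surgery and 60, 90 and 180 days postoperative".
- Counter movement jump: "It is performed at 90 and 180 days postoperative".
- ACL-RSI: "Participants answer a total of 12 questions on the 10-point scale from 0 to 100 1–7 days before surgery", then at 30, 60, 90 and 180 days.

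None of these lists t1.

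**The concern.** A change score needs a value from before treatment. For these five outcomes no participant has one. Multiple imputation, which the same section plans, cannot recover a variable that was observed in nobody. As written, the confirmatory analysis of strength, jumping, dynamic balance and psychological readiness does not exist.

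The gap would have to be closed later. One way is to treat the first available visit as baseline. Under Study procedure the training runs until reconstruction, and under Outcomes t2 is the primary time point. So t2 is a follow-up, and subtracting it would remove the very effect that the trial was designed to detect. The Aims section expects the group difference to be largest early and to fade, and in that pattern a change from t2 gives the most misleading answer. Leaving this choice open until data are in hand does not fit a confirmatory label.

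**Working it through.** **1. Visits by outcome, from the outcome sections**

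| Outcome | Visits | t1 value? | Comparisons |
|---|---|---|---|
| KOOS | t1, t2, t4–t7 (t3 unclear) | yes | 5 or 6 |
| Range of motion | t1–t5 | yes | 4 |
| Active leg raise | t1–t4 | yes | 3 |
| Tegner score | t1, t2, t4–t7 | yes | 5 |
| Isokinetic strength | t6, t7 | no | 2 |
| Counter movement jump | t6, t7 | no | 2 |
| Heel lift | t2, t5–t7 | no | 4 |
| Y-balance | t2, t5–t7 | no | 4 |
| ACL-RSI | t2, t4–t7 | no | 5 |
| Workability | absence days, time to full work | no change form | not counted |

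**2. Share affected**

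- Outcomes: 5 of 10.
- Comparisons without a baseline: 2 + 2 + 4 + 4 + 5 = 17.
- Comparisons with a baseline: 5 + 4 + 3 + 5 = 17, or 18 if KOOS is also taken at t3.
- Share: 17/34 = 50%, or 17/35 = 49%.

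The counts depend on the unit. Splitting tests by muscle, speed or direction changes both numerator and denominator. The secure statement is five outcomes.

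**3. What a substitute baseline would do (hypothetical)**

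If t2 served as baseline, the estimated contrast at a later visit would be

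(group difference at that visit) − (group difference at t2).

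The three t2 comparisons would vanish. The other 3 + 3 + 4 = 10 comparisons for heel lift, Y-balance and ACL-RSI would be measured from t2. For isokinetic strength and the jump, only a change from 90 to 180 days could be formed, which discards any difference already present at 90 days.

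For illustration, assume a t2 difference of 0.533 SD, borrowed from the sample size section, and a fraction f of it remaining later. The true difference is 0.533f and the change from t2 gives 0.533(f − 1):

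| f | True difference (SD) | Change from t2 (SD) |
|---|---|---|
| 1.25 | +0.67 | +0.13 |
| 1 | +0.53 | 0 |
| 0.75 | +0.40 | −0.13 |
| 0.5 | +0.27 | −0.27 |
| 0.25 | +0.13 | −0.40 |

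With 57 per arm and an assumed within-person correlation ρ, the standard error in SD units is √(2(1 − ρ)) × √(2/57). This is 0.187 for ρ = 0.5 and 0.145 for ρ = 0.7. The chance of a significant result favouring the comparator is Φ(|change|/SE − 1.96):

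- f = 0.5: 30% (ρ = 0.5) to 45% (ρ = 0.7).
- f = 0.25: 57% to 79%.

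In both cases guided training is still truly better.

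**4. Primary outcome**

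The plan's own figure reproduces. d = 8/15 = 0.533, and the exact two-sample t calculation at 2.5% one-sided and 80% power gives 57 per arm, 114 in total (power 80.6%). KOOS has a t1 value by the primary hypothesis, so neither its analysis nor this number depends on the point raised here.

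**The case against.** The strongest reply is that this is one over-general sentence in a condensed article. The staged schedule looks deliberate: the abstract says that the tests become more demanding over time, and nobody would ask a freshly injured patient to jump. An analyst would see at once that no change score can be computed, so silent error is unlikely. Every affected outcome is secondary. A separate analysis plan may give details by outcome.

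Much of this stands. The schedule is not at fault, and the primary result is not at risk. But the point is not a missing detail. The article states a rule for every outcome and labels the analyses confirmatory, and the visit times contradict that rule. The general remark under Outcomes about seven time points does not help, because each outcome section sets its own narrower list.

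A reader might infer that the plan will use t2 or the 90-day visit as baseline, and so will reverse the effect in half of its comparisons. The documents do not support that. No section names either visit as baseline, and Aims and Outcomes treat t2 as a follow-up. With t2 as baseline, reversal could concern only the 10 later comparisons of heel lift, Y-balance and ACL-RSI, and only if the difference shrinks. A constant difference would cancel to zero and a growing one would be understated.

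Whether the leg-raise grade or return-to-sport success needs an ordinal or binary model is detail commonly left to an analysis plan, and is not part of this point.

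**Conclusion.** The point holds. The prescribed dependent variable is undefined for five secondary outcomes: isokinetic strength, counter movement jump, heel lift, Y-balance and ACL-RSI. That is 5 of about 10 outcomes and about half of the outcome-by-visit comparisons. The certain consequence is that the stated confirmatory analysis cannot be carried out for them. Bias or sign reversal is a conditional risk that depends on how the gap is later filled.

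This should be corrected, but it does not undermine the trial's main conclusion. The KOOS comparison from t1 to t2 and the sample size of 114 stand.

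The conclusion assumes that the schedule figures, which are not shown, agree with the visit times in the text. The illustrative effect sizes and probabilities also assume the KOOS effect size for other outcomes, within-person correlations of 0.5 to 0.7 and equal variances across visits. The finding itself does not need them.

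**What to change.** Amend the Statistical analysis section as follows:

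- Limit change from baseline, or baseline-adjusted analysis, to outcomes measured at t1.
- For isokinetic strength, counter movement jump, heel lift, Y-balance and ACL-RSI, make the observed value at each visit the dependent variable. A limb symmetry index may serve for the limb tests, but not for ACL-RSI, which is a questionnaire.
- Compare groups at each visit, adjusting for covariates recorded at t1 such as age, gender and activity level, which the section already names.
- State that t2 is a follow-up for every outcome and never a baseline or an adjustment covariate.

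Randomisation supports a comparison of observed values without a baseline. What is lost is the precision that a baseline of the same measure would have added. The cost is wording only: no new visit, no new data and no added burden for participants. The change should be made before outcome data are examined by group.
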